### Endocrine function

Endocrine hormone concentrations (cholecystokinin and peptide YY) are quantified by radioimmunoassay and gamma counter (Packard Cobra II Auto Gamma), Meso Scale Discovery multiplex panels (ghrelin, glucagon-like peptide-1, plasminogen activator inhibitor-1, adiponectin and leptin) and with the Cobas® e411 instrument (insulin). Blood specimens are collected in vacutainers containing EDTA plus protease inhibitor additives: DPPIV inhibitor (dipeptidyl-peptidase IV inhibitor (Millipore, St. Charles, MO, USA) 10 μl/ml whole blood) and aprotinin (G-Biosciences, St. Louis, MO, USA) 240 KIU/ml whole blood). In addition, for the ghrelin aliquot, a 1 M HCl (Trace Metal Grade HCl, Fisher-Scientific, Pittsburg, PA, USA) solution is added (100 μl/ml plasma) prior to plasma storage at −80C.

Plasma glucose and lipid concentrations and serum non-esterified fatty acid concentrations are measured using the Cobas® Integra® 400 plus.

### Genomics and transcriptomics

Genomic DNA is isolated from whole blood (8 mL) using Qiagen© PAXgene Blood DNA kits and purified genomic DNA is aliquoted and stored at -80 °C until use. Single nucleotide polymorphisms in the genes of interest will be analyzed using TaqMan® SNP Genotyping Assays (ThermoFisher Scientific) performed on a QuantStudio® 7 Flex Real-Time PCR System (ThermoFisher Scientific) according to the manufacturer’s instructions. Allelic discriminations will be performed using Genotyper™ software (ThermoFisher Scientific). All ambiguous genotypes will be repeated in independent PCR experiments.

Transcriptomic profiling of whole blood is planned for a subset of participants to assess systemic immune activation. The Tempus™ blood RNA collection tube and the Tempus™ Spin RNA isolation kit (ThermoFisher Scientific) is used to stabilize and to isolate RNA.

### Nutrient status

Plasma carotenoid levels are quantified by liquid chromatography-diode array detection. Plasma homocysteine, thiamin, vitamin B6 and red blood cell riboflavin levels are quantified by liquid chromatography-fluorescence detection. Plasma vitamin B12 and folate status are analyzed by electrochemiluminescence immunoassay on Cobas®e411 analyzer.

Concentrations of trace minerals including iron, zinc, and copper are determined by Inductively Coupled Plasma-Optical Emission Spectrophotometry (Vista, Agilent Technologies). Blood is collected using Sarstedt Lithium Heparin polypropylene tubes.

### Clinical chemistry

Specimens required for clinical laboratory panels are submitted to the University of California Davis Medical Center clinical laboratory following the specified collection requirements. Comprehensive metabolic panels are determined by automated chemical analyzer. Complete blood count with differential analysis is quantified by Coulter count.

### Cognitive testing

The Wechsler Abbreviated Scale of Intelligence™ Vocabulary and Matrix Reasoning modules are administered to assess cognitive function. A trained interviewer leads the assessments and records the responses given without providing indication of performance. The WASI®-II Stimulus Book is placed directly in front of the respondent to provide visual prompts for each task. The interviewer provides a standard set of instructions and begins when the participant is ready. Responses are scored by the interviewer in real-time according to published instructions for both modules. The T score, intelligence quotient, and 95% confidence interval are calculated according to published instructions.

The Cambridge Neuropsychological Test Automated Battery® is administered to assess cognitive function, including executive function. CANTAB® eclipse™ 5 software by Cambridge Cognition Ltd. is licensed on a touch screen tablet computer to complete each of the following four modules: 1) Motor Screening, 2) One Touch Stockings of Cambridge, 3) Spatial Working Memory, and 4) Stop Signal Task. Trained study personnel will provide instructions and brief demonstrations according to the standard instructions for each module before the participant is tested.

Examination of decision-making is performed using The Iowa Gambling Task™ by Psychological Assessments Resources, Inc. The computer-based game is run using Inquisit 3 Lab software [19]. Trained study personnel read a scripted introductory statement, providing all of the required instructions. Participants are asked to complete the task on their own; study personnel step out of the testing room until the participant indicates that the task is complete.

### Eating behavior

Eating behaviors and motivations are assessed by questionnaire and food preference activities. The Yale Food Addiction Scale addresses addictive eating behaviors reported over the past 12 months, particularly with high-fat/sugar foods [10]. The Food Choice Questionnaire assesses nine motives related to food choice: 1) health, 2) mood, 3) convenience, 4) sensory appeal, 5) natural content, 6) price, 7) weight, 8) familiarity, and 9) ethical concern [12]. The Three-Factor Eating Questionnaire is used to measure: 1) ‘cognitive restraint of eating’, 2) ‘disinhibition’, and 3) ‘hunger’ [13].

Implicit and explicit wanting of foods is assessed using a paired foods test, which is based on the Implicit Associations Test [20]. A forced-choice paired comparison paradigm presents paired images of foods side-by-side on a computer screen. Participants are asked to select the food that they most want to eat by pressing either the L or D key on a standard keyboard, corresponding to the food image on the right or left of the screen, respectively. The food preference activity is administered only once, at approximately 1.5 h postprandial, with respect to the timing of consumption of the mixed macronutrient challenge meal. Study personnel provide instructions for the assessment, but are not present as it is being completed. This computerized task is designed to measure implicit liking and wanting of four classifications of foods: high-fat and sweet, high-fat and savory, low-fat and sweet, low-fat and savory. As part of this task, images of single food items are presented individually to determine explicit liking of particular foods. Participants are instructed to indicate how much they like the taste of a single food item by clicking a location along an electronic visual analog scale that is presented below the image of the single food item on the computer screen.

### MindWare mobile impedance cardiograph

Heart rate variability, respiration variability, and sympathetic nervous system activity as measured by skin conductance, is collected using the MindWare hardware and software systems by MindWare Technologies LTD. Data is monitored in real-time for the majority of one research visit day by wireless data transmission or captured locally on the collection device worn by the participant. Electrodes are placed in seven identified locations on the torso, five on the front torso and two on the back. Locations are predetermined by the manufacturer. Men are asked to shave the placement sites according to a provided diagram before the study visit. Trained study personnel clean skin at the application site using sterile alcohol prep pads and wipe dry using gauze before placing the torso electrodes. Two additional electrodes are placed on the non-dominant hand using only water to clean the hand locations. Data is acquired using the MindWare system for 15 min before and immediately after the two study challenges: 1) mixed macronutrient dietary challenge and 2) emotional recall challenge. Participants are asked to sit quietly during these dedicated data collection/rest periods without access to mobile devices or reading materials. Data is continuously collected throughout the morning and early afternoon, in addition to the described data collection/rest periods.

### Emotional challenge

The Profile of Mood States questionnaire is administered before and immediately after the anger recall task. Participants are asked to remember, relive, and vividly recall a negative event that occurred within the last six months that makes them feel extremely angry. A paper and pen are provided for taking notes and recording details of the memory for a period of 2 min. The participant is then asked to share the experience aloud with a study staff member for 3 min.

### Taste thresholds

Threshold concentrations of perceived taste of salty, sweet, and bitter flavors are assessed by a forced choice masked taste test. Solutions of varying concentrations of sodium chloride, sucrose, and caffeine, respectively, are prepared using distilled water at room temperature. Sensitivity to salty taste is assessed using five concentration levels: 1) 0.5 g/L, 2) 1.75 g/L, 3) 6 g/L, 4) 21 g/L, and 5) 75 g/L (approximately 10 times the concentration in chicken broth). Perception of sweet taste is assessed using five levels of sucrose concentration: 1) 1.23 g/L, 2) 3.7 g/L, 3) 11 g/L, 4) 33 g/L, and 5) 99 g/L (similar to the concentration found in regular soft drinks). Threshold of detection of bitter taste is assessed using five concentrations of caffeine in distilled water: 1) 0.16 g/L, 2) 0.25 g/L, 3) 0.40 g/L, 4) 0.64 g/L, and 5) 1.01 g/L (similar to the concentration in brewed coffee).

Solutions are presented to study participants in increasing order, starting with the most dilute and increasing in concentration until three consecutive concentrations are correctly identified. Samples are provided in clear, plastic cups labeled with randomly generated code numbers. The participant is instructed to rinse the mouth with distilled water before each round of tastings. Each round consists of three taste cups; one cup contains the tastant (solution) and two identical clear plastic cups that contain fresh distilled water only. The participant is asked to record the unique identifiers on each of the three cups presented at each round and then to select which solution is different from the other two. The participant records the three-digit number identifying the odd cup and if taste distinction is not possible, the participant is instructed to guess which solution is different. Participants may spit the taste solution out or swallow it, depending on preference, and are provided with more sample volume to taste, if requested. Sample cups are removed after each round and study personnel record the identifier of the selected cup behind a wall to determine if the taste solution was correctly identified. The lowest concentration correctly identified in a series of three consecutive correctly identified solutions is determined to be the threshold of detection.

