### Secondary hypotheses

Secondary endpoints are grouped into three categories: metabolic/physiologic impacts, neurocognitive function, and diet/lifestyle/personal characteristics. Each category is defined below according to the list of dependent variables to be included. Selected secondary a priori hypotheses are numbered following each category definition and identified by the independent variable of interest. Directionality of the hypothesized association may vary according to each independent/dependent variable combination and therefore, the expected direction of the independent variable is reported in the numbered section and the expected direction of the dependent variable is reported in the category definition (e.g. higher diet quality will be associated with higher insulin sensitivity and lower glucose concentration), see below.

The metabolic/physiologic category includes: higher insulin sensitivity, substrate switching, production of short-chain fatty acids, breath hydrogen and methane, subjective satiety, and pulmonary function; and lower glucose concentration, peripheral arterial tone, risk of dysbiosis of the gut microbiota, gut inflammation, systemic immune activation, systemic inflammation, fatty acid profiles, oxygenated metabolites, endocannabinoids, bile acid profiles, hepatic lipogenesis, triglyceridemia, appetitive hormones, and taste threshold.Higher diet quality (e.g. according to the Healthy Eating Index), modified by genotype, will be associated with metabolic/physiologic phenotypes.Healthy eating behaviors (health-related food choices motives and non-addictive eating behaviors) will be associated with metabolic/physiologic phenotypes.Dysbiosis and gut inflammation will be associated with metabolic/physiologic phenotypes.Lower postprandial bile acid responses will be associated with metabolic/physiologic phenotypes.Lower postprandial plasma fatty acid concentrations will be associated with metabolic/physiologic phenotypes.

The neurocognitive function category includes higher executive function, healthy eating behaviors, and stress system responsiveness, and lower chronic stress, allostatic load, heart rate variability, respiration variability, and nerve conductivity.

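### The taste-test scoring rule can return only levels 1 to 3 of five, so a true threshold at level 4 or 5 can never be scored correctly, and correct guesses push scores down

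*Protocol article*

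**What the plan says.** The section on taste thresholds in the protocol article sets out the whole procedure. Each tastant has five levels: "Sensitivity to salty taste is assessed using five concentration levels" (0.5, 1.75, 6, 21 and 75 g/L), "Perception of sweet taste is assessed using five levels of sucrose concentration" (1.23, 3.7, 11, 33 and 99 g/L), and "Threshold of detection of bitter taste is assessed using five concentrations of caffeine in distilled water" (0.16, 0.25, 0.40, 0.64 and 1.01 g/L).

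Each round has three cups, one with tastant and two with water. Guessing is required: "if taste distinction is not possible, the participant is instructed to guess which solution is different". Testing proceeds upward, "starting with the most dilute and increasing in concentration until three consecutive concentrations are correctly identified". The score is then defined: "The lowest concentration correctly identified in a series of three consecutive correctly identified solutions is determined to be the threshold of detection".

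The section describes no level above the fifth, no repeat round at a level and no allowance for guessing. Under the secondary hypotheses, taste threshold is a dependent variable in the metabolic/physiologic category, among those expected to be lower: "hepatic lipogenesis, triglyceridemia, appetitive hormones, and taste threshold".

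**The concern.** The rule needs three successive correct levels and scores the lowest of them. The two top concentrations can therefore confirm a threshold but can never be one. A participant who first tastes caffeine at 0.64 g/L, or sucrose at 33 g/L, has a true threshold on the tested ladder that the score cannot express.

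Forced guessing adds an error in one direction. A lucky answer just below the true threshold joins the run and lowers the score. Under perfect detection, nothing offsets this by raising it.

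The outcome is to be related to diet quality, eating behaviour, gut dysbiosis, bile acids, fatty acids, physical activity and stress. If it is analysed as a five-level threshold, its upper end is not observed. How participants without a run are handled then decides whether the least sensitive tasters contribute at all.

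**Working it through.** The document gives no score range or error rate for this test, so there is no figure of its own to reproduce.

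**Inputs from the section on taste thresholds.** Five levels per tastant; ascending order; one three-cup round per level, so a guess is correct with probability 1/3; stop at three consecutive correct levels; threshold = lowest level of that run.

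**Step 1: the cap (no assumption needed).** The possible runs are 1-2-3, 2-3-4 and 3-4-5, so the score is level 1, 2 or 3. All three runs contain level 3, so a wrong answer there leaves no run whatever the other answers are.

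| Tastant | Recordable (g/L) | Not recordable (g/L) | Full ladder | Recordable range |
|---|---|---|---|---|
| Salt | 0.5, 1.75, 6 | 21, 75 | 75/0.5 = 150-fold | 6/0.5 = 12-fold |
| Sucrose | 1.23, 3.7, 11 | 33, 99 | 99/1.23 ≈ 80-fold | 11/1.23 ≈ 8.9-fold |
| Caffeine | 0.16, 0.25, 0.40 | 0.64, 1.01 | 1.01/0.16 ≈ 6.3-fold | 0.40/0.16 = 2.5-fold |

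**Step 2: guessing.** Assumption: the probability of a correct answer is 1/3 below the true threshold and 1 at or above it. Write p1 to p5 for the five levels. For the first run of three:

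- score 1: p1·p2·p3
- score 2: (1 − p1)·p2·p3·p4
- score 3: (1 − p2)·p3·p4·p5
- no run: the remainder

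Example, true level 4 (p1 = p2 = p3 = 1/3, p4 = p5 = 1): score 1 = 1/27; score 2 = (2/3)(1/9) = 2/27; score 3 = (2/3)(1/3) = 6/27. The sum is 9/27 = 1/3, and no run is 2/3.

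Example, true level 5 (p1 to p4 = 1/3, p5 = 1): score 1 = 3/81; score 2 = (2/3)(1/27) = 2/81; score 3 = (2/3)(1/9) = 6/81. The sum is 11/81, and no run is 70/81.

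| True threshold | Score 1 | Score 2 | Score 3 | No run | Too low |
|---|---|---|---|---|---|
| Level 1 | 1 | 0 | 0 | 0 | 0 |
| Level 2 | 1/3 | 2/3 | 0 | 0 | 33.3% |
| Level 3 | 1/9 | 2/9 | 2/3 | 0 | 33.3% |
| Level 4 | 1/27 | 2/27 | 2/9 | 2/3 (66.7%) | 33.3% |
| Level 5 | 1/27 | 2/81 | 2/27 | 70/81 (86.4%) | 13.6% |
| Above level 5 (all guesses) | 1/27 | 2/81 | 2/81 | 74/81 (91.4%) | 8.6% |

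These figures agree with an exact enumeration of all 2^5 = 32 answer patterns.

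**Step 3: imperfect detection.** The document gives no detection rate; 90% at and above threshold is assumed for illustration. For a true level 3: score 1 = (1/3)(1/3)(0.9) = 0.10; score 2 = (2/3)(1/3)(0.9)² = 0.18; score 3 = (2/3)(0.9)³ = 0.486. No run = 1 − 0.766 = 0.234, or about 23%. The absence of a run therefore does not prove a threshold above level 3.

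**Step 4: where the cap could bite.** The document compares the top salt level with about ten times chicken broth, so broth is about 7.5 g/L and level 3 is 6/7.5 = 80% of it. Sucrose level 3 is 11/99 = one ninth of the level likened to soft drinks. Caffeine level 3 is 0.40/1.01 ≈ 40% of the level likened to brewed coffee, on a ladder whose steps are only about 1.6-fold.

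**The case against.** The strongest reply is that levels 4 and 5 are there to confirm a threshold at level 3, and that few people need more. By the document's own comparisons, missing level 3 salt means not telling something close to broth from water. That is a fair point for salt and, less strongly, for sucrose. It is weaker for caffeine. It also amounts to saying that the scale has three levels with censoring above them, which the section does not state.

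Second, three in a row is itself the guard against guessing: someone who guesses throughout gets a false threshold only 8.6% of the time. That stands. The rule does not, however, stop a single lucky guess just below the true threshold from lowering the score.

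Third, a reader might infer that participants without a run are set to missing and that this biases the associations with diet and eating behaviour. The article supports neither step. It does not say how such participants are coded, a detail that an article may leave to a fuller plan, and it says that analysis-specific statistical plans will follow. Nor does it allow the direction or size of any bias to be worked out. Those inferences are not part of this point. The cap remains, because no coding of participants without a run can make the stated rule return level 4 or 5.

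**Conclusion.** The point holds as a fault in a rule that is stated in full. The recorded threshold can only be level 1, 2 or 3; this follows from the wording alone. No participant with a true threshold at level 4 or 5 can be scored correctly: each gets either no value or one that is too low. The probabilities in the second table depend on perfect detection at and above threshold and on a 1/3 guess rate.

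It would go too far to say that insensitive tasters are generally recorded as sensitive. At a true level 4, the most frequent false score is level 3 (22%), with 7% at level 2 and 4% at level 1.

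The documents do not give the share of participants with thresholds at level 4 or above, so the effect on the study cannot be computed. The cap is most plausible for caffeine. The matter concerns one of many secondary endpoints and leaves the primary outcomes and the sample size untouched. Severity is minor to moderate.

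**What to change.** Keep the test as run and change how it is described and analysed.

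- State that the rule resolves only levels 1 to 3.
- Keep participants without a run of three in the analysis.
- Analyse the round-by-round answers with an ordinal or interval-censored threshold model that has a guessing probability of 1/3 and a lapse rate for errors above threshold.
- As a sensitivity analysis, treat participants without a run as a top ordered category above level 3.
- Do not assign level 4 or 5 from a partial run. That would credit a lucky guess at level 5 and misplace someone who erred only at level 3.

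The top-category coding should not be the main analysis, because under the assumed 90% detection about 23% of true level-3 tasters would be placed there wrongly.

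The cost is modest. Staff record the selected cup after each round, so the answers should exist and no new testing is needed. The downside is some extra analysis work and a lapse rate that must be estimated or assumed; if assumed, results should be shown over a range of values.

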### Skin reflectance

Skin reflectance is assessed using a Konica-Minolta Spectrophotometer CM-2500d as described previously [21]. The instrument is placed flat against the skin in three locations: 1) back of hand, in the area between the index finger and thumb, 2) inside of the upper arm, and 3) upper center of the forehead. Measurements are taken in duplicate and averaged.

### Endothelial function

Peripheral endothelial vasodilation responses to reactive hyperemia are assessed using an EndoPAT 2000 (endothelial peripheral arterial tone) [22] as a non-diagnostic indicator of endothelial function. The participant lies supine on a bed with legs uncrossed and must rest for 10–15 min. A blood pressure cuff is placed on the non-dominant upper arm and fit snuggly above the elbow. The wrists and forearms rest on arm supports positioned at a comfortable distance based on arm length. The index finger of each hand is placed in a probe that is positioned in a designated socket of the arm support. The probe covers inflate in order to ensure connectivity between the tip of the finger and the wire probe. A soft anchor is placed on the finger adjacent to the probe finger and the tubing is looped to avoid contact with the hand. The participant must lie still in order to produce a stable baseline period of data for at least 5 min. The upper arm blood pressure cuff is inflated to 200 mmHg and is kept at that pressure to occlude the brachial artery for 5 min. After 5 min, the blood pressure cuff is released and deflates quickly. The participant remains resting for 5 min post-occlusion. The reactive hyperemia index score is calculated as the post-to-pre occlusion PAT signal ratio on the occluded side, normalized to the control side and corrected for baseline vascular tone (Itamar Medical Ltd).

## Statistical analysis

### Sample size calculations

The sample size calculation is designed to detect a potentially small correlation between dietary variables and our primary outcomes, i.e. systemic immune activation and metabolomics responses to a mixed macronutrient challenge meal. In order to explain approximately 3% of the variation in inflammation, we need to detect a correlation coefficient (R) = 0.18 (R^2^ = 0.032 ≈ 3%). Establishing 95% power and α = 0.05 level of significance, the target sample size is 22 in each of the 18 categories defined by age, sex, and BMI. In addition, we aim to enroll an additional 10% of the calculated sample size to account for attrition.

